**Figure 1 F1:**
[figure not shown]
Hypothetical pathway of the interplay between chronic viruses, immune activation, systemic inflammation, endothelial activation and vasculopathy. CIMT, carotid intima-media thickness; IL-6, interleukin-6; PWV, pulse wave velocity; VL, Viral Load; HLA-DR, Human Leukocyte Antigen-DR isotype; IFNγ, interferon gamma; TFNα, Tumour Necrosis Factor alpha; ICAM-1, intercellular adhesion molecules-1 and hsCRP, high-sensitivity C-reactive protein.

In addition to HIV, there is compelling evidence that reactivation of latent herpesviruses may be an important cause of vasculopathy. In HIV-uninfected elderly populations from high-income settings, latent cytomegalovirus (CMV) infection drives dysregulation of cell-mediated immunity,^15 27–29^ not dissimilar to what is described in HIV-associated immune activation.^29^ CMV and other viral proteins have been found in atherosclerotic plaques.^20^ Varicella zoster virus (VZV) can directly infect the vascular endothelium to cause vasculitis and subsequent stroke and was found to be the most common opportunistic infection (prevalence 15%) in a study of HIV-infected patients with stroke in Malawi.^12^ The seroprevalence of herpesviruses is high in SSA,^30^ particularly in HIV-infected populations.^16^

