### Study objectives

This study will test the hypothesis that immune activation and dysfunction, driven by HIV and reactivation of latent CMV/VZV herpesvirus infections, lead to increased CBD/CVD risk in adults aged ≥35 years in SSA. We will address this through the following objectives:

To determine if progression of the surrogate marker of CBD/CVD or occurrence of new-onset vasculopathy is higher in adults aged ≥35 years with HIV infection on ART compared with those without HIV.To determine if progression of surrogate markers of CBD/CVD or occurrence of new-onset vasculopathy is higher in adults aged ≥35 years with HIV/herpes viral antigenaemia or chronic immune activation compared with those without HIV/herpes viral antigenaemia or chronic immune activation. Specifically, we will determine if progression of surrogate markers or new-onset vasculopathy is higher in the following:In ART patients with reactivated latent herpes viral infection, compared with those without reactivated latent herpes viral infection.In ART patients with the highest 25% of markers for immune activation, inflammation or endothelial activation compared with the bottom 25%.In ART patients with incomplete virological suppression or virological resurgence of HIV, compared with those with suppressed HIV plasma viral load.

The secondary study objectives are to determine if viral antigenaemia or chronic immune activation increases the occurrence of the following clinical events: (1) stroke, (2) MI, (3) angina (excluding MI), (4) peripheral vascular disease (PVD), (5) all-cause death/vascular-related death and (6) immune reconstitution inflammatory vasculopathy.

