### Measurement of soluble markers of immune activation using multiplex bead array

A custom-made multiplex assay will be used to assess soluble markers of monocyte activation (CD163), systemic inflammation (IL-6) and endothelial activation (intracellular adhesion molecule 1) in plasma, isolated from blood samples of HIV-uninfected and HIV-infected ART initiators. Following isolation, plasma will be aliquoted and stored at −80°C until further use.

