## Outcomes

### Primary outcomes

The primary outcomes are the progression of surrogate markers of CBD/CVD, namely PWV and CIMT, as well as the occurrence of new-onset vasculopathy defined by threshold values outlined in table 2.

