For objective 2b, we will again fit a set of GLMs, with change from baseline in PWV as response variable, this time to investigate if, in HIV-infected ART patients, there is an association between progression of vasculopathy and immune activation and inflammation biomarkers (IL-6, Intracellular adehesion molecule [ICAM], CD163). Specifically, for each marker, we will regress PWV on marker quantiles. After having built models for each marker, we will then develop comprehensive multiple regression models for PWV and CIMT with multiple independent markers as predictor variables.

For objective 2c, we will proceed as for objective 2a, but comparing HIV-infected ART patients with incomplete virological suppression or virological resurgence of HIV with those with suppressed HIV plasma viral load.

In addition to these analyses, given the repeated measurements for PWV, immune activation and inflammation markers, we will extend the GLMs for PWV to linear mixed models taking full account of the longitudinal nature of the data. Mixed models will also handle deviations from the visit schedule in a principled fashion and use all available data for dropouts. If a log link function is required for PWV in the GLMs, we will fit marginalised models using Generlaised Estimating Equations [GEE] instead of Linear Mixed Models [LMMs].

For the secondary study objectives, we will use univariate methods to assess the frequency of clinical events within exposure strata. If there are sufficient numbers of clinical events, we will develop Poisson or negative binomial regression models (depending on model fit) for each clinical event type to compare exposure-defined participants.

We will also use time-to-event models, specifically Cox proportional hazard models, to investigate associations between all-cause mortality and exposures.

As part of exploratory analyses, we will aim to identify risk groups that are potentially incompletely captured with the measured exposure variables. We will perform unsupervised group-based multitrajectory modelling of multivariate longitudinal patient trajectories to confirm any associations we have found using more traditional approaches.^44^

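### Objective 2b: the single-marker models are specified for PWV only, so the high-versus-low contrast of each marker is not estimated for CIMT progression, a primary outcome

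*Protocol article*

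**What the plan says.** Under Primary outcomes, the protocol article puts the two surrogates on an equal footing: "The primary outcomes are the progression of surrogate markers of CBD/CVD, namely PWV and CIMT". Table 2 defines progression for each as the change from baseline to 24 months.

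Under Study objectives, 2b concerns progression of surrogate markers, in the plural, and states the comparison: "In ART patients with the highest 25% of markers for immune activation, inflammation or endothelial activation compared with the bottom 25" per cent.

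Under Sample size and statistical analysis, the 2b models are generalised linear models "with change from baseline in PWV as response variable", and the text then specifies that "for each marker, we will regress PWV on marker quantiles". The markers named are IL-6, ICAM and CD163. CIMT appears for the first time in 2b in the next step, which is to build "comprehensive multiple regression models for PWV and CIMT with multiple independent markers as predictor variables".

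The laboratory section labels CD163 as a marker of monocyte activation, IL-6 of systemic inflammation and ICAM-1 of endothelial activation. The Figure 1 legend describes a "Hypothetical pathway of the interplay between chronic viruses, immune activation, systemic inflammation, endothelial activation and vasculopathy".

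**The concern.** The question in 2b is a contrast between patients high and low on a given marker. The article specifies a model for that contrast for PWV and not for CIMT. For CIMT the only stated 2b model contains several markers at once, so its coefficients describe each marker with the others held fixed.

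The two quantities can differ a good deal when the markers are causally linked. If IL-6 acts on the carotid wall partly by way of endothelial activation, a model that also contains ICAM-1 leaves only the remainder for IL-6. A small IL-6 coefficient for CIMT could then be read as no association, when the association 2b asks about had not been estimated. The study intends to point to inflammatory targets for later intervention, so that reading would matter.

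**Working it through.** **1. Which response each stated model names**

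| Analysis | PWV | CIMT |
|---|---|---|
| Objective 1, change on HIV status | yes | yes |
| Objective 2a, on CMV and VZV titres | yes | yes |
| Objective 2b, one marker at a time, by quantile | yes | not named |
| Objective 2b, several markers together | yes | yes |
| Objective 2c, proceeds as 2a | yes | yes |
| Longitudinal extension (mixed models or GEE) | yes | not named |

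Objective 2b is the only objective whose main models drop one of the two primary outcomes. No other stated analysis fills the gap. The longitudinal extension is for PWV. The simple regressions planned for the baseline analysis relate exposures and outcomes measured at baseline, so they are cross-sectional and say nothing about progression.

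**2. Whether the joint model can stand in**

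The documents give no correlations between markers and no marker effects, so any size is an illustration under assumed values. Take the order CD163, then IL-6, then ICAM-1, then change in CIMT, with all variables standardised. Let a be the link between successive markers, c the effect of ICAM-1 on change in CIMT, and d a direct effect, equal for CD163 and IL-6. Then:

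- CD163 alone: d + a·d + a²·c
- IL-6 alone: d + a·c + a·d
- ICAM-1 alone: c + a·d + a²·d
- All three together: d, d and c

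With c = 0.25:

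| a | d | CD163 alone | IL-6 alone | ICAM-1 alone | Joint: CD163, IL-6, ICAM-1 |
|---|---|---|---|---|---|
| 0.3 | 0 | 0.02 | 0.08 | 0.25 | 0, 0, 0.25 |
| 0.5 | 0 | 0.06 | 0.13 | 0.25 | 0, 0, 0.25 |
| 0.7 | 0 | 0.12 | 0.18 | 0.25 | 0, 0, 0.25 |
| 0.3 | 0.10 | 0.15 | 0.21 | 0.29 | 0.10, 0.10, 0.25 |
| 0.5 | 0.10 | 0.21 | 0.28 | 0.33 | 0.10, 0.10, 0.25 |
| 0.7 | 0.10 | 0.29 | 0.35 | 0.37 | 0.10, 0.10, 0.25 |

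For example, at a = 0.5 and d = 0.10, IL-6 alone is 0.10 + 0.5 × 0.25 + 0.5 × 0.10 = 0.275. A simulation of the same chain with 1,000,000 records agrees with these values to within sampling error.

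**3. What this does to detection, under the same assumptions**

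Take n = 800 × 0.8 = 640 (the planned HIV-infected sample after the stated 20% loss) and a two-sided test at 0.05. With a = 0.5 and d = 0, IL-6 is detected with probability 89% alone and 5% jointly. With direct effects, joint detection of IL-6 at a = 0.3, 0.5 and 0.7 is:

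- d = 0.05: 23%, 18%, 12%
- d = 0.10: 69%, 56%, 36%
- d = 0.15: 96%, 90%, 71%

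The range of 12% to 96% shows that the result is driven by a value the documents do not supply.

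**4. Stated figures**

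The point disputes no figure in the article. The sample size is built on new-onset vasculopathy and is unaffected.

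**The case against.** The strongest reply is that this is condensation. The text is a journal article, every other objective covers both outcomes, and the step before the joint models speaks of having built models for each marker. The authors may well intend single-marker CIMT models. That is plausible. But the article does state a response variable for 2b, states it twice, and both times it is PWV. If the omission is only drafting, one sentence settles it.

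A second reply concerns the pathway, and much of it stands. The figure is not shown, its legend speaks of interplay, and the Introduction lists monocyte activation and the IL-6 pathway as features of one immune state, without an order between them. The order used above is an inference from the legend and the laboratory labels. The reference to independent markers may also mean a non-redundant subset, which would lessen the problem. The missing CIMT contrast does not depend on any of this.

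A third reply is that single-marker estimates have a weakness of their own, and it is correct. With d = 0.10 and a from 0.3 to 0.7, IL-6 alone gives 0.21 to 0.35 against a total effect (d + a·c) of 0.18 to 0.28, because CD163 confounds it. This is a reason to keep the joint model beside the single-marker models.

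A reader might go further and infer that every marker is over-adjusted for CIMT, or that marker effects on CIMT are never estimated at all. Neither follows. ICAM-1 is last in the inferred order, so adjusting it for the other two is control of confounding. The joint model does estimate conditional associations, and the baseline regressions can give a cross-sectional one.

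**Conclusion.** The gap is real and rests on stated text: for 24-month change in CIMT, no model described in the article estimates the high-versus-low contrast of a single marker that objective 2b poses. That part needs no assumption about biology.

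The further consequence is conditional. If the markers lie in the inferred order, the joint model takes out the part of the CD163 and IL-6 associations that passes through ICAM-1. The direction is clear but the size is not. The fall to zero under full mediation is true by construction, and with direct effects the loss runs from slight to large. It would be wrong to conclude from the documents that IL-6 will be reported as null for CIMT. The supportable statement is that a small joint coefficient could not be read as an answer to 2b.

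**What to change.** Add one sentence to the objective 2b analysis: the single-marker quantile GLMs for IL-6, ICAM and CD163 will be fitted to 24-month change in CIMT in the same way as to change in PWV. With quarters as the quantiles, this gives the contrast named in the objective for both primary outcomes.

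Keep the multi-marker models, and describe their coefficients as associations conditional on the other markers in the model.

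The cost is three further regressions. Table 1 already schedules CIMT at baseline and 24 months, and the soluble markers at baseline, 6 and 12 months, so no new measurement is needed.

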## Patient public involvement

The global burden of HIV-associated CBD and CVD has tripled over the last two decades with the greatest impact in SSA. CBD and CVD are a priority for patients in Malawi as HIV infection is endemic and the population are living for longer. Knowledge of this informed our research question with the aim of understanding the mechanisms and thus direct targeted novel therapies to reduce this burden. Patients will be involved in the recruitment of the study, but not in the design. Patients and their advisors will be thanked for contributing to the study.

## Ethics and dissemination

Written informed consent will be obtained from all study participants, either written or witnessed verbal consent with thumbprint if the participant is non-literate. Study data will be maintained in an encrypted and password-protected database to which only study staff will have access. Study participants who develop a clinical event will be managed, using the hospital guidelines, by our study clinician alongside the hospital doctor. Clinical data will be anonymised using unique identifying code. Study data will be kept for 10 years and then destroyed with a record, as recommended by good clinical practice guidelines. Results of the main trial and each of the secondary endpoints will be submitted for publication in a peer-reviewed journal.

## Discussion

African regions continue to bear the brunt of HIV infection. In 2013, an estimated 8.5 million adults were receiving ART.^45^ As the landscape evolves, this population will live longer with stable HIV infection but likely remain at an increased risk of CBD/CVD compared with HIV-uninfected individuals of similar age and sex. This study will be the first to determine the extent to which HIV reactivation of herpesvirus infection and inflammation contribute to CBD/CVD risk in an adult African population starting ART. The results of this work could potentially open avenues for novel anti-inflammatory and antiviral interventions for the primary prevention of CBD/CVD in HIV populations in Africa.
